DTG is well tolerated with only 2% to 3% of patients discontinuing the drug for adverse events in phase III trials. Frequent side-effects include sleep disturbance, gastro-intestinal complaints, headache, and respiratory tract complaints; most were grades 1 or 2 in clinical trials (13, 14). No life threatening adverse events were observed. Rates of psychiatric adverse events, i.e. insomnia, anxiety, depression or suicidality, were low in treatment-naïve phase III/IIb trials of DTG with frequency of withdrawal as low as 5% (51). However, observational studies have reported higher rates of central nervous system side effects (up to 20%) in treatment-naïve or -experienced patients receiving DTG (52, 53) with discontinuation rates due to central nervous system adverse events from 0.6% to 3.4% (52, 54-56). A retrospective cohort study in the Netherlands reported up to 13.7% of discontinuation rate due to adverse event on DTG (57) and another in Germany found that women and older patients were more at risk of discontinuing DTG for neuropsychiatric side effects (58). DTG is also lipid neutral with fewer elevations of low-density lipoprotein of grade 2 or higher compared to efavirenz or boosted darunavir in the SINGLE and FLAMINGO trials (12, 59). However, there are no data on the effect of DTG on body fat composition and the associated cardiovascular risk or bone mass density, which are growing concerns in our aging HIV population.

Drug interactions are very few (43), another advantage of the compound. DTG is a substrate of UGT1A1, CYP3A4, UGT1A3, and UGT1A9. Only 1% of potential drug-drug interactions are considered to be at risk (Figure 2). DTG should be used at the dose of 50mg twice daily with rifampicin, a potent inducer of UGT1A1 and CYP3A4. Co-administration with other inducers of UGT1A1 and CYP3A4 such as carbamazepin, oxcarbamazepin, phenytoin, phenobarbital and St. John's wort should be avoided. As DTG inhibits the renal transporter OCT2, it is contraindicated with the antiarrhythmic dofetilide (which is not authorized in Switzerland) and caution is needed when co-administered with metformin. DTG should be taken with food when administered with calcium or iron supplementation or vitamins intake as well as with magnesium or aluminium-containing antacids (14).

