### 5.2 Secondary Outcomes

1. Proportion of patients maintaining HIV suppression defined as HIV-RNA <50 copies/ml throughout 48 weeks (+/- 21 days). A single blip defined as HIV-RNA <200 copies/ml during the study period is allowed as long as this value is followed by HIV-RNA <50 copies/ml;
2. Proportion of patients with HIV-RNA < 50 cp/ml at week 48 by FDA snapshot analysis; Proportion of patients experiencing loss of future drug options defined as new intermediate or high-level resistance to one or more drugs to which the patient's virus was considered sensitive at trial entry;
3. Time to loss of virological response (TLOVR) up to week 48 defined as the first of the two-confirmed HIV-RNA >100 copies/ml (at least two weeks apart);
4. Change in CD4 cell count from baseline to week 48 +/- 21 days;
5. Change in HIV-DNA level from baseline to week 48 +/- 21 days;
6. Change in lipidic profile (total cholesterol, high density lipoprotein-cholesterol, triglycerides, and low density lipoprotein-cholesterol) from baseline to week 48 +/- 21 days;
7. Change in glucose profile from baseline to week 48;
8. Change in Framingham-calculated cardiovascular risk from baseline to week 48;
9. Change in glomerular function rate from baseline to week 48;
10. Proportion of patients with an adverse event throughout week 48;
11. Proportion of patients with a serious adverse event (SAE) throughout week 48;
12. Proportion of patients with a CNS adverse event throughout week 48;
13. Proportion of patients new to DTG with CNS symptoms at 2 and 6 weeks after starting DTG;
14. Change in patients' health-related quality of life from baseline to weeks 12 and 48;
15. Assessment of patient's monitoring satisfaction from baseline to weeks 24 and 48 for patients in the patient-centered monitoring arm;
16. Assessment of the global satisfaction of the monitoring at week 48 for all patients (regardless of the randomisation arm);
17. Proportion of patients in the patient-centered monitoring arm expressing willingness to change monitoring options throughout 48 weeks;
18. Assessment of patient's treatment satisfaction at week 48;
19. Assessment of ARV treatment in the post study;
20. Study satisfaction at week 48;
21. Cost-effectiveness of study arms at 48 weeks;
22. Changes in patient weight from baseline to week 48.

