- Glomerular function rate changes: measurement of plasma creatinine at the sites' local chemistry laboratories and calculation according to the CKD-EPI (Chronic Kidney Disease Epidemiology Collaboration) equation using the following online calculator: <http://www.qxmd.com/calculate-online/nephrology/ckd-epi-egfr>. A printout of the result should be filed with the source documents.
- Occurrence of adverse events: documentation in the electronic CRF by the study nurse or other (e.g. study coordinator, research associate).
- Occurrence of serious adverse events (SAE): documentation in the electronic CRF by the study nurse or other (e.g. study coordinator, research associate).
- Occurrence of CNS adverse events: documentation in the electronic CRF (log AE) by the study nurse or other (e.g. study coordinator, research associate).
- Presence of CNS symptoms: documentation in the electronic CRF (week 2 and 6 CNS questionnaire) by the study nurse or other (e.g. study coordinator, research associate).
- Weight changes: documentation in the electronic CRF by the study nurse or other (e.g. study coordinator, research associate).
- Health-related quality of life: assessment using the PROQOL-HIV instrument (87, 88) and a visual analog scale. These assessments will be performed at baseline, week 12 and week 48 by the study nurse/physician. The PROQOL-HIV questionnaire can be filled-in directly by the patient. Documentation on paper source document and transfer into the electronic CFR by the study nurse or other (e.g. study coordinator, research associate).
- Patient's monitoring satisfaction. Assessment using:
  - o Monitoring choice, for patients randomized in the patient-centered monitoring arm);
  - o Visual analogue scale (for all patients regardless of the randomization arm),
  - o Proportions of patients in the patient-centered monitoring arm expressing the willingness to change of monitoring option
- Patient's treatment satisfaction: assessing using visual analogues scale, patient's preferences about treatment, ARV regimen chosen for the post-study period and reason for change in case of change.
- Study satisfaction: assessment using 7 questions discussed at week 48.

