### 9.2.4 Assessment of Safety Outcomes

#### 9.2.4.1 Adverse Events

At every study visit starting from the randomization in the trial, i.e. from the baseline visit, we will record adverse event information (i.e. type of event, date of onset, duration, final outcome, action to be taken, assessment of severity, relationship with study drug(s) and/or procedure). For the definition and procedures, we are referring to section 10. CNS side effects will be recorded using a standardized questionnaire at week 2 (by phone call) and week 6 among patients new to DTG drug and reported as adverse events as well. Assessment of adverse events will be standardized in the CRF.

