#### 10.1.1. Definition and assessment of (Serious) Adverse Events and other safety related events

An **Adverse Event (AE)** is any untoward medical occurrence in a patient or a clinical investigation participant administered a pharmaceutical product and which does not necessarily have a causal relationship with the study procedure. An AE can therefore be any unfavourable and unintended sign (including an abnormal laboratory finding), symptom, or disease temporally associated with the use of a medicinal (investigational) product, whether or not related to the medicinal (investigational) product.

Adverse Events that need to be reported in this study are listed in the Adverse Event list (see Appendix 6). This list will be used starting from the baseline visit to confirming the absence or presence of any listed adverse event. Spontaneous, non-serious Adverse Events that are not listed in the Appendix 6 list will be collected in the patient's medical file according to local usual practice but will not be reported into the study-related document. Laboratory abnormalities listed in the Adverse Event list, will be reported as Adverse Events if they are at least a grade 3 and if they appear after randomization in the study (i.e. starting from the baseline visit). In case of laboratory abnormality already present before the randomisation, this will be considered as an adverse event only in case of worsening.

A **Serious Adverse Event (SAE)** is classified as any untoward medical occurrence that:

- results in death,
- is life-threatening,
- requires in-patient hospitalization or prolongation of existing hospitalisation,
- results in persistent or significant disability/incapacity,
- results in a congenital anomaly/birth defect, or
- is an important medical events that may not be immediately life-threatening or result in death, or require hospitalisation, but may jeopardise the patient or may require intervention to prevent one of the other outcomes listed above should also usually be considered serious. Examples of such events are intensive treatment in an emergency room or at home for allergic bronchospasm, blood dyscrasias or convulsions that do not result in hospitalisation, or development of drug dependency or drug abuse.

SAEs should be followed until resolution or stabilisation. See details in section 10.1.3.

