##### *Clinical assessments:*

- ART changes since previous visit and reasons for changes;
- Current treatment satisfaction;
- Monitoring options changes since previous visit and reasons for changes;
- Current monitoring satisfaction;
- Number, date and value of HIV-RNA performed since previous visit;
- Number, date and results of genotypes resistance testing performed since previous visit\*;
- Grade 3 or 4 AE, SAE and pregnancy occurrence since previous visit (reported yearly);
- Quality of life questionnaire and visual analogues scale;
- Adherence questionnaire\*;
- Patient's weight and blood pressure\*.

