### **Objectives and Outcomes**

The overall objective of the post-study is to evaluate the long term efficacy, feasibility and acceptance both of the DTG+FTC dual strategy and of the options of a patient-centered monitoring as an observation without any intervention.

Secondary Outcomes related to the post-study:

1. Proportion of patients maintaining HIV suppression;
2. Proportion of patients experiencing loss of future drug options;
3. Time to loss of virological response (TLOVR);
4. Change in CD4 cell count from;
5. Change in lipidic profile;
6. Change in glucose profile;
7. Change in Framingham-calculated cardiovascular risk;
8. Change in glomerular function rate;
9. Proportion of patients with an adverse event of grade 3 or 4;
10. Proportion of patients with a severe at least one serious adverse event (SAE);
11. Proportion of patients with a CNS adverse event;
12. Changes in patient weight;
13. Change in patients' health-related quality of life;
14. Assessment of ART changes during post-study;
15. Assessment of patient's treatment satisfaction;

16. Assessment of option for monitoring changes during post-study;
17. Assessment of patient's monitoring satisfaction;
18. Number of viral load performed yearly;
19. Patient adherence to treatment.

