### **Statistical analysis**

Secondary Outcomes related to the post-study will be analyzed as described in section 11 for the 96 and 144 week time-points.

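### Post-study outcome 11 counts CNS adverse events with no grade limit, but after week 48 only grade 3/4 and serious events are collected, so it cannot be measured as worded

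*Protocol*

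**What the plan says.** **Up to week 48.** Section 5.2, item 12, lists "Proportion of patients with a CNS adverse event throughout week 48", and Section 5.4, item 8, repeats it as a safety outcome. Neither gives a grade. Section 9.2.2 gives the source: "Occurrence of CNS adverse events: documentation in the electronic CRF (log AE) by the study nurse or other". Section 9.2.4.1 has adverse events recorded at every visit from baseline. It adds, for patients new to dolutegravir, that "CNS side effects will be recorded using a standardized questionnaire at week 2 (by phone call) and week 6", and that these findings are also reported as adverse events. Section 10.1.1 limits reporting to events on the Appendix 6 list. The only grade threshold it states is for laboratory findings: "Laboratory abnormalities listed in the Adverse Event list, will be reported as Adverse Events if they are at least a grade 3".

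**After week 48.** The clinical assessments for weeks 96 and 144 in Section 13 contain one adverse event item: "Grade 3 or 4 AE, SAE and pregnancy occurrence since previous visit (reported yearly". The table in Section 13 and the synopsis row on post-study follow-up carry the same grade restriction. No CNS questionnaire is scheduled.

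**Outcome and analysis after week 48.** Among the post-study outcomes, item 9 (adverse events) is limited to grade 3 or 4. Item 11 is "Proportion of patients with a CNS adverse event", without a limit. The analysis is set by reference: "Secondary Outcomes related to the post-study will be analyzed as described in section 11 for the 96 and 144 week time-points".

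**Background.** Of dolutegravir's frequent side effects, Section 3.2 says "most were grades 1 or 2 in clinical trials".

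**The concern.** The outcome keeps its label and its analysis across week 48 while the recording rule behind it changes. Non-serious grade 1-2 CNS events first occurring after week 48 have no place in the data, yet item 11 as worded includes them. A table giving the proportion with a CNS adverse event at weeks 48, 96 and 144 would put unlike quantities side by side.

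Section 3.7 describes side effects as relatively uncommon except for CNS events in observational studies, so readers will look at this outcome for long-term tolerability. A low figure at week 96 or 144 could be taken for good tolerability when part of it comes from what was recorded. A statistical analysis plan cannot repair this afterwards, because it cannot recover events that were never collected.

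**Working it through.** The protocol states no figure for this outcome, so there is none to reproduce. The check compares the two recording rules, with an illustration of scale.

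**1. The two rules side by side**

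| | Baseline to week 48 | Weeks 96 and 144 |
|---|---|---|
| Outcome | CNS adverse event, no grade limit (5.2 item 12) | CNS adverse event, no grade limit (Section 13 item 11) |
| Events recorded | Listed clinical events, no grade threshold stated (9.2.2, 10.1.1) | Grade 3/4 and serious events only (Section 13) |
| Timing | Every study visit | Once a year, since the previous visit |
| CNS questionnaire | Weeks 2 and 6, patients new to dolutegravir | None |

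The outcome is the same in both columns and the data are not.

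**2. Is there another source after week 48?**
- Extraction from the cohort database is marked by an asterisk in Section 13. The adverse event row has no asterisk.
- Section 10.1.3 follows events already ongoing at week 48. It does not capture new ones.
- The post-study quality-of-life questionnaire is not an adverse event record.

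No source for new non-serious grade 1-2 CNS events was found.

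**3. What each form of the proportion would show**
- Per period: the intervals are 48 weeks each (48 - 0, 96 - 48, 144 - 96), so length does not explain a difference. The later two omit grades that the first includes, so they are understated relative to the wording.
- Cumulative from baseline: the proportion cannot fall in a fixed group of patients. It would add grade 3/4 or serious events after week 48 to events of any grade before it.

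Section 13 does not say which form is meant. Neither gives the outcome as worded.

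**4. Scale, as an illustration only**

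Recorded per-period proportion = p × f. Here p is the true any-grade proportion of patients, and f is the share of those patients with a grade 3/4 or serious event. Section 3.2 reports CNS side effects of up to 20% in observational studies, so p = 20% is an upper figure; p = 10% is an assumption. The protocol gives no f, so 5% to 40% is assumed. Counts use the 92 patients planned per treatment group; fewer may consent to the post-study.

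| p | True count of 92 | f = 5% | f = 10% | f = 20% | f = 40% |
|---|---|---|---|---|---|
| 20% | 18.4 | 1% (0.9) | 2% (1.8) | 4% (3.7) | 8% (7.4) |
| 10% | 9.2 | 0.5% (0.5) | 1% (0.9) | 2% (1.8) | 4% (3.7) |

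Recorded counts of 92 are in brackets.

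**5. Sensitivity of the between-arm comparison**

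This uses a two-sided 5% normal-approximation test with 92 per group: power = Φ[(d - 1.96·s0)/s1], where d is the difference, s0 the pooled standard error and s1 the unpooled one.
- 20% against 10%: d = 0.10, s0 = √(2 × 0.15 × 0.85/92) = 0.0527, s1 = √((0.16 + 0.09)/92) = 0.0521; power about 48%.
- 2% against 1% (the same contrast with f = 10% in both arms): d = 0.01, s0 and s1 both about 0.0179; power about 8%.

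**The case against.** **No before-and-after comparison is planned.** Section 11.4.2 compares CNS adverse events between treatment groups and between monitoring groups, and after week 48 all arms share one recording rule. This stands. A reader might infer that the gap favours DTG + FTC over cART; the documents do not support that. What the planned comparison loses is sensitivity.

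**The proportion need not fall.** It is tempting to say that the post-study proportion falls by construction. That would need a per-period proportion, which Section 13 does not specify, and even then it assumes the true rate does not rise. Read as item 12 of Section 5.2 carried forward, the proportion is cumulative and cannot fall. It would still mix two rules.

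**All-grade recording before week 48 is an inference.** It rests on the absence of a threshold for clinical events in Section 10.1.1. It covers only events on the Appendix 6 list, which is not shown. This stands as a limit on the contrast. It does not affect the main point, which needs only the wording of item 11 and the post-study collection rule.

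**Item 11 can be read as CNS events among those collected.** That is a charitable reading and possibly the intended one. However, item 9 in the same list states its grade limit and item 11 does not, so the text does not say it.

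**It is a minor outcome.** Item 11 is one of 19 secondary outcomes in an observational follow-up, and Section 3.7 names virological failure as the main risk. This is fair, and it keeps the point modest.

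**Conclusion.** The inconsistency is real. Post-study item 11 promises CNS adverse events without a grade limit, and the post-study visits collect only grade 3/4 and serious ones. Reported as worded, the outcome would omit non-serious grade 1-2 CNS events after week 48. It would be understated if given per period and of mixed definition if cumulated. The harm is to comparison over time and to sensitivity. The primary outcomes and the week 48 CNS outcome are unaffected.

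The size is not known. A reader might infer from the remark in Section 3.2 that the recorded proportion would be some 10% to 20% of the true one. That only restates an assumed share of grade 3/4 events. The remark covers sleep, gastro-intestinal, headache and respiratory complaints together, says only that most were grade 1 or 2, and gives no split for CNS events. The illustration also holds the true rate constant. That is uncertain, because the CNS questionnaires target the first weeks on dolutegravir and Section 13 lets patients and physicians choose the regimen from week 48.

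**What to change.** Reword post-study item 11 as the proportion of patients with a grade 3/4 or serious CNS adverse event, matching item 9 and what is collected. Whenever weeks 0-48 and later periods appear together, apply that definition to weeks 0-48 as well. Do not cumulate the any-grade outcome of Section 5.2, item 12, past week 48.

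Report changes of antiretroviral therapy for CNS reasons separately, under post-study item 14; the reasons for change are already collected at weeks 96 and 144. They should not be joined to item 11 as a composite. Switches are restricted up to week 48 (Sections 7.4 and 8.1.2) and open to choice afterwards (Section 13), so a composite would itself change meaning at week 48.

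The change is to wording and tabulation only and needs no new visit or data item. The price is fewer events and so an imprecise estimate, which should be presented descriptively.

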### **Statistical analysis**

Secondary Outcomes related to the post-study will be analyzed as described in section 11 for the 96 and 144 week time-points.

## **14. PUBLICATION AND DISSEMINATION POLICY**

The final data will be presented at one or more scientific meetings and published in scientific journal(s). No patient data will be presented that could permit identification of any individual study participant. Publication of data derived from this protocol will be supervised by the Sponsor/Investigator and by the Principal Investigator(s) in conjunction with all study investigators. No publication will be made without prior approval of the Sponsor/Investigator and Principal Investigator(s).

## **15. FUNDING AND SUPPORT**

### **15.1 Funding**

This trial has received funding from the Swiss National Science Foundation. The funding application, review and approval documents as well as the approved budget are stored online (on [mysnf.ch](http://mysnf.ch)) and a copy filed in the trial master file.

Any potential additional funding from SHCS or other institution will be notified to the leading Ethic Committee.

### **15.2 Other Support**

The study will be performed within the SHCS network using the local infrastructure of all participating sites.

Nested sub-studies are possible. In such cases the leading Ethics Committee will be notified.

## **16. INSURANCE**

Insurance will be provided by the Geneva University Hospitals. A copy of the insurance confirmation will be filed in each investigator site file and the trial master file. The insurance certificate is filed at the legal office of the HUG.

## **17. STUDY AGREEMENT**

The present Protocol acts as an Agreement between all participating Study Sites and the Sponsor. The Protocol represents a legal document especially for Study Sites with whom the Sponsor does not have a separate Study Site Agreement, such as Zurich.

## **19. APPENDIX**

1. Patient information and consent form
2. Protocol flyer
3. Case report form : worksheets and logs
4. Patient logbook: patient diary
5. List of interaction with dolutegravir
6. Adverse Event list
7. Information letter of 25.May.2018 to the Ethics Committee
8. Communication of 25.May.2018 to the DSMB

## 20. SUPPLEMENTARY FILES

### SF1: Summary of presented or published studies on DTG monotherapy

| Study                                                                                                                | Details                                                                                                                                                                                                                                                                                                    | Results                                                                                                                                                                                                                                                                                                                                                                                                                                                                                                                                       | Comments                                                                                                                     |
|----------------------------------------------------------------------------------------------------------------------|------------------------------------------------------------------------------------------------------------------------------------------------------------------------------------------------------------------------------------------------------------------------------------------------------------|-----------------------------------------------------------------------------------------------------------------------------------------------------------------------------------------------------------------------------------------------------------------------------------------------------------------------------------------------------------------------------------------------------------------------------------------------------------------------------------------------------------------------------------------------|------------------------------------------------------------------------------------------------------------------------------|
| Retrospective analysis of treatment experienced patients who switched to DTG monoT ( ROJAS )           | N = 33; HIV duration, 19 years (IQR: 17–23); HIV suppression, 8 years (IQR: 4–13); 40% with history of AIDS                                                                                                                                                                                                | 32/33 <37 copies/mL at W24; no change in viral dynamics at levels <37 copies/mL                                                                                                                                                                                                                                                                                                                                                                                                                                                               | 1 case of viral rebound in complex patient with INSTI-experience and poor adherence; included INSTI mutation 118R at week 24 |
| Single-arm observational pilot switch in treatment- experienced patients ( Katlama )                   | N = 28; HIV duration, 20 years; HIV suppression, 6 years (IQR: 3–8)                                                                                                                                                                                                                                        | 25/28 <50 copies/mL at W24;
24/25 <20 copies/mL                                                                                                                                                                                                                                                                                                                                                                                                                                                                                            | 3 cases of viral rebound in patients with prior INSTI experience, but with good adherence. All <50 cp/mL with triple therapy |
| Retrospective data from case notes in treatment- experienced patients switched to DTG monoT ( Gubavu ) | N = 52 (N = 21 monotherapy); follow-up, W27 (IQR: 24–40)                                                                                                                                                                                                                                                   | 21/21 remained <50 cp/mL                                                                                                                                                                                                                                                                                                                                                                                                                                                                                                                      | No cases of viral rebound                                                                                                    |
| Single-arm observational pilot study ( pilot for DOMDONO )                                                    | N = 5 experienced pts                                                                                                                                                                                                                                                                               | 4/5 remained undetectable                                                                                                                                                                                                                                                                                                                                                                                                                                                                                                                     | Viral rebound included possible drug interaction with multivitamins.                                                         |
| RCT, 48W switch study in experienced pts ( DOMONO )                                                    | N = 104 pts on cART for 40 months with CD4 nadir of 340; randomized to immediate switch to DTG monotherapy or deferred switch after 24W                                                                                                                                                                    | Confidential (see e-mail by [name] 21.1.20): when 77/96 on DTG monoT pts had reached W48 of monotherapy, VF had developed in 8 (2 before W24, 6 after W24) . This led to the premature study discontinuation. Although DTG monoT was non-inferior to cART at W24, VF continued to occur after W24 and led to DTG resistance in 3 . Final results at CROI 2017                                                                                                                                                     |                                                                                                                              |
| RCT in experienced pts with VL <50 cp/mL on current ART ( DOLAM )                                      | N = 450; randomized 1:1:1 to DTG, DTG + 3TC, or current treatment (control). Follow-up at BL, 4, 12, 24, 36, 48W.

Pts on stable triT with <50 cp/mL in ≥2 consecutive determinations for ≥12 months, no prior VF or resistance mutations to 3TC/FTC or INSTI, nadir CD4 >200cells/mm  . | Confidential (see e-mail by [name] on 9.2.2017): 2 VF in monoT arm at the end of phase A (90 pts, 24W follow-up). According to DSMB advise (called according to protocol safety rules “DSMB will review the data if the proportion of confirmed virological failure in any of the experimental arms reaches ≥5%”), the Steering Committee has decided to interrupt the DTG arm and to continue the DOLAM study with two arms: CONTROL and DTG+3TC (no safety issues in dualtherapy arm). Results expected after October 2017 |                                                                                                                              |
| Single-arm, open-label switch study in                                                                               | N = 8 experienced pts, fully enrolled.                                                                                                                                                                                                                                                              | Confidential: 4 pts already at W24,                                                                                                                                                                                                                                                                                                                                                                                                                                                                                                    | Final results expected in June 2017                                                                                          |

|                                                                                                                               |                                                                                       |                                                                                            |                                                                                    |
|-------------------------------------------------------------------------------------------------------------------------------|---------------------------------------------------------------------------------------|--------------------------------------------------------------------------------------------|------------------------------------------------------------------------------------|
| patients with VL <50 copies/mL ( MONODO )                                                                              | Follow-up 24W                                                                         | 1pt at W20, 3 pts at ≤W12, no VF                                                           |                                                                                    |
